### Adverse event reporting and harms

Any adverse events (AEs) reported by participants, such as falls, illness or skin irritation from the activPAL or Fitbit, will be recorded within the trial database during the study. At the 3 month and 9 month post randomisation timepoints, participants will complete a questionnaire asking if they have experienced a fall, relapse or AE since their last point of contact in the study. If a participant reports an AE directly to their study site, a delegated staff member will report it to the Principal Investigator and central research team for it to be recorded within the trial database. Data recorded on AEs will include date of onset, resolution, outcome, severity and causality. Expectedness and cause (probable, possible, unlikely or unrelated to the trial) of the AE will be assessed by the Principal Investigator or the central research team.

Serious adverse events (SAEs) (AEs which are life-threatening, resulting in hospitalisation, death or prolonged and worsened impairment) should be reported to the Chief Investigator by the site Principal Investigator or researcher within 24 hours of becoming aware of the event. The Chief Investigator will be responsible for notifying the trial Sponsor of an SAE within 48 hours and the NHS Research Ethics Committee that gave a favourable opinion of the research within 15 days of becoming aware of the event. A ‘directly attributable’ SAE will only be recorded and reported if the event occurs during contact time with an intervention deliverer or while undertaking physical activity as part of the intervention. Participants who experience an SAE that affects their continued safety or significantly affects the conduct or outcomes of the study will be withdrawn.

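### The rule for recording 'directly attributable' SAEs conflicts with the unrestricted SAE rules beside it and makes attribution depend on what the participant was doing at onset

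*Protocol article*

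**What the plan says.** All the relevant sentences stand in one section of the protocol article, Adverse event reporting and harms.

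- **AE recording.** AEs that participants report, "such as falls, illness or skin irritation from the activPAL or Fitbit, will be recorded within the trial database during the study". The follow-up rule at 3 and 9 months is that "participants will complete a questionnaire asking if they have experienced a fall, relapse or AE since their last point of contact in the study".
- **Causality.** Cause is graded on four levels: "Expectedness and cause (probable, possible, unlikely or unrelated to the trial) of the AE will be assessed by the Principal Investigator", or alternatively by the central team. Causality is among the data items held for each AE.
- **SAE reporting.** SAEs are defined as a subset of AEs. Each one "should be reported to the Chief Investigator by the site Principal Investigator or researcher within 24 hours of becoming aware of the event". For the sponsor, the rule is: "The Chief Investigator will be responsible for notifying the trial Sponsor of an SAE within 48 hours". The ethics committee is to be told within 15 days.
- **Restriction.** The section then says that a *directly attributable* SAE "will only be recorded and reported if the event occurs during contact time with an intervention deliverer", or else during physical activity that belongs to the intervention.

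**The concern.** The last of these rules does not fit the others. The AE and SAE rules set no condition on when or where an event begins. The restriction does, and it applies to the events of most interest in a safety assessment: serious ones attributed to the intervention.

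Two things are at stake. Site staff have conflicting instructions for a serious event that they judge probably related but that began after the activity had ended. In addition, if the trial reports a number of *directly attributable* SAEs, that number reflects circumstances at onset and not the assessor's judgement of cause. The Trial Steering Committee is charged with monitoring patient safety, and readers will look for such a count.

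**Working it through.** No figure in the plan needs reproducing. The check sets the sentences side by side and applies them to one case.

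**Test case.** An intervention participant is admitted to hospital after a fall some hours after a walk taken towards a step goal. The assessor grades the cause as probable.

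| Rule in the section | Applied to the test case |
|---|---|
| Any reported AE is recorded | Recorded |
| Cause is graded on four levels | Graded probable |
| SAEs go to Chief Investigator (24 h), sponsor (48 h) and ethics committee (15 days) | Reported |
| *Directly attributable* SAE only if onset is in contact time or during intervention activity | Condition not met |

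The first three rows agree with each other. The fourth can be read in two ways.

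1. **As a limit on recording and reporting.** If the event is regarded as directly attributable, the fourth rule says not to record or report it, while the first and third say to do both. An SAE graded unrelated meets no such restriction. The most related events therefore get the narrowest rule.
2. **As a definition of a label.** The event is recorded and reported under the general rules but cannot carry the label, although its cause was graded probable. Any count of labelled events omits it. Such omissions can only lower the count, so the bias is downward.

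**How far each limb reaches.** Inputs are from the sections iStep-MS consultations, iStep-MS intervention and Study design.

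- *Contact limb:* four sessions of 45–60 min. 4 × 45 = 180 min = 3 h, and 4 × 60 = 240 min = 4 h. Planned contact is 3–4 hours per participant, the last at about week 11, with follow-up to 9 months.
- *Activity limb:* this is wider, because the intervention targets everyday stepping and sitting and so can include unsupervised activity. The documents give no hours for it. It still requires onset while the activity is under way.
- *After month 3:* the intervention is stated to last 3 months, which leaves 9 − 3 = 6 months of follow-up. The handbook and tracker are also meant to support maintenance afterwards, and the last consultation sets long-term goals. Whether activity in those 6 months counts as part of the intervention is not stated.

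**The case against.** The strongest reply is that nothing need be lost. SAEs are a subset of AEs, any reported AE is recorded with a causality grade, and the 3- and 9-month questionnaires ask about falls, relapses and other AEs over the whole interval. The disputed term appears in quotation marks and is no level of the causality scale, so the sentence may only define a label. The reporting chain to the Chief Investigator, sponsor and ethics committee would then be untouched, and related SAEs could still be counted from the grades.

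Much of this stands, and it rules out three stronger conclusions that a reader might draw.

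- *That delayed harms will be missing from the database.* The general AE rule and the questionnaires should still capture many of them.
- *That the timing condition replaces the causality assessment.* The text does not say so; the grade is still collected.
- *That the 3–4 contact hours, set against 9 months, measure the problem.* They cover only one limb and leave out the activity limb, which is wider and not quantified.

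Nor are there three mutually incompatible rules: the 24-hour rule and the causality grading are compatible with each other.

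The reply does not remove the conflict. The sentence says when an event is recorded and reported, not merely how it is named, so the label reading has to be supplied by the reader. Even on that reading, attribution turns on circumstance at onset. This is also not detail that a condensed article has left to a fuller document, because the article states a restrictive rule that disagrees with its neighbours.

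**Conclusion.** The sentence is wrong as written. On the literal reading it contradicts the unrestricted AE and SAE rules. On the milder reading it excludes related SAEs with later onset from the attributable count and so biases that count downward.

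The contradiction follows from the text alone. The bias rests on two assumptions: that a count of *directly attributable* SAEs will be used or reported, and that some related SAEs begin outside contact or activity. Its size cannot be given, since the documents contain no SAE rates, no activity hours and no distribution of onset times. The total number of SAEs recorded need not be affected.

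The point concerns safety reporting only. It does not touch the primary outcome, the sample size or the efficacy analysis.

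**What to change.** Amend the section so that one rule applies:

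1. Every SAE in either arm, from randomisation to 9 months, is recorded and reported along the existing chain, whatever the time or place of onset.
2. The timing condition is removed as a criterion both for recording and for attribution. If the sponsor wants to know whether an event began during a session or activity, that can be a descriptive data field.
3. Any count of related SAEs is based on the four-level causality grade already collected, with the levels that count as related stated in advance. The term *directly attributable* is either dropped or defined by that grade.

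The cost is a short amendment and possibly a few more SAE reports. The causality scale, the database and the reporting chain already exist.

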### Patient and public involvement

Patient and public members contributed to the development of this research through advising on aspects related to study design, participant recruitment, data collection and intervention delivery. A Public Advisory Group comprising PwMS and healthcare professionals will advise the research team during the trial on matters relating to direction of the research, participant-facing documents and the public dissemination strategy.

## Ethics and dissemination

This study received ethical approval from the College of Health, Medicine and Life Sciences, Brunel University of London (reference 50434-NHS-Feb/2025-53 798-2) and the NHS London—Bloomsbury Research Ethics Committee (reference 25/LO/0272).

Dissemination to academic audiences will include scientific journal publications and presentations at conferences. The findings will be disseminated to the public and relevant stakeholders via newsletters, a dedicated University Webpage and the MS Society website. To maximise reach and impact of the study findings, dissemination materials will be made open access.

### Data access statement

Datasets generated and/or analysed during the current study will be stored in a publicly available repository: https://brunel.figshare.com/. Quantitative data will be made available for a minimum of 10 years following data analysis. To protect participant confidentiality, supporting focus group transcripts will not be made publicly available.
